### Outcome

#### Primary outcome

##### The daily consumption of methadone

Daily consumption of methadone from baseline to the 2nd, 4th, 6th and 10th weeks will be presented. One primary outcome measure will be the change in the daily consumption of methadone from baseline to the 6th week. The enrolled patients will go to the clinic to receive methadone every day, and the dosage will be strictly administered by the doctor, which will be recorded in the clinic computer system.

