##### The visual analogue scale for drug craving

The other primary outcome will be the determination of drug craving using a visual analogue scale for drug craving on which the participants will mark on a 100-mm line in proportion to their craving from 0 (no craving) to 100 (strong craving) [21]. The degree of craving will be marked by the subjects at baseline and the 2nd, 4th and 6th weeks after acupuncture administration and at the post-treatment follow-up visit in the 10th week.

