### Sample size calculation

The primary outcome measure for drug craving is VAS. Based on previous studies [5, 30], after 4 weeks of treatment, the VAS for drug craving score difference between the baseline and the endpoint in the sham acupuncture group should be approximately 20 ± 30, while the true acupuncture group should be approximately 37.5 ± 28. Type 1 error is assumed at 0.05, and type 2 error is assumed at 0.1. PASS11.0 software (CSS Statistical Software, Kaysville, UT, USA) has been used to determine the sample size, and the minimum sample size is 60 subjects for each group. Considering a dropout rate of 15%, a total of 140 subjects will be required with 1:1 allocation to each group (70 participants per group) for this study.

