### Statistical analysis

All analyses will be conducted based on the intention-to-treat principle and per-protocol (PP) analysis. Missing data will be replaced according to the principle of multiple imputations. Descriptive statistics will be presented for each group as the mean change (SD, 95% confidence intervals). All statistical tests will be analysed by using the SPSS statistical software version 20 (IBM SPSS Statistics, New York, USA). *P* values < 0.05 (two-sided) are considered statistically significant. Demographic and baseline data will be tabulated and evaluated using analysis of variance (ANOVA) or the *χ*^2^ test. To compare means between two groups, we will use the independent sample *t* test. Two-way repeated-measures analysis of variance (ANOVA) will be carried out to explore time × treatment interaction (“time” is the unit of measurement).

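### Group means are compared by a t test that does not adjust for baseline; the test is valid, but ANCOVA on data already collected would be more precise and robust to chance baseline imbalance

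*Protocol article*

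**What the plan says.** All statements are from the protocol article.

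- **Between-group test.** Under Statistical analysis: "To compare means between two groups, we will use the independent sample" t test. Neither a baseline covariate nor a baseline-adjusted model is named there or elsewhere in the article.
- **Summary measure.** The same section says "Descriptive statistics will be presented for each group as the mean change (SD, 95% confidence intervals").
- **Repeated measures.** A two-way repeated-measures ANOVA "will be carried out to explore time × treatment interaction".
- **Methadone primary.** "One primary outcome measure will be the change in the daily consumption of methadone from baseline to the 6th week".
- **Craving primary.** "The degree of craving will be marked by the subjects at baseline and the 2nd, 4th and 6th weeks", and again at the week-10 follow-up.
- **Secondary scales.** SF-36, PSQI, BDI-II and BAI each have a baseline assessment.
- **Sample size.** The calculation uses the baseline-to-endpoint difference in VAS after 4 weeks of treatment: 20 ± 30 in the control arm and 37.5 ± 28 in the acupuncture arm. "Type 1 error is assumed at 0.05, and type 2 error is assumed at 0.1". The result is 60 per group, raised to 70 for 15% dropout.

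**The concern.** The baseline value usually predicts the follow-up value, and here it is collected for every continuous outcome. A t test on change uses it with a fixed coefficient of 1. Unless the correlation is perfect, that coefficient is too large, and two things follow.

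- The estimate keeps variance that a fitted coefficient would remove.
- A chance baseline difference between arms moves the estimate in the opposite direction. Randomisation is in blocks of 4, and the article states no stratification by baseline craving or dose, so nothing in the design limits that difference except sample size.

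The article also plans to test baseline data between groups but says nothing about what follows if a difference appears. Any adjustment made at that stage would be chosen after seeing the data.

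**Working it through.** **1. Reproduce the plan's figure.** Inputs from the Sample size calculation section: difference 37.5 − 20 = 17.5; SD = √((30² + 28²)/2) = 29.02; two-sided alpha 0.05; power 0.90. The normal formula gives 58 per group and the exact noncentral t gives 59. The stated 60 is consistent with this. Power at 60 per group is 90.6% (noncentral t). These inputs are for VAS *change*, so they match a t test on change scores.

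**2. Variance of the two analyses.** Let σ be the SD at baseline and at follow-up (assumed equal) and r their correlation.

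- Change score: 2σ²(1 − r)
- ANCOVA residual: σ²(1 − r²)
- Ratio: (1 − r²) / (2(1 − r)) = (1 + r)/2

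**3. Put numbers in.** The document gives no r, so the values below are assumptions. The change SD is held at 29.02 and the difference at 17.5, with 60 per group. ANCOVA SD = 29.02 × √((1 + r)/2).

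| r (assumed) | Variance reduction | ANCOVA SD | VAS power |
|---|---|---|---|
| t test on change | – | 29.02 | 90.6% |
| 0.3 | 35% | 23.39 | 98.2% |
| 0.5 | 25% | 25.13 | 96.6% |
| 0.7 | 15% | 26.75 | 94.4% |
| 0.8 | 10% | 27.53 | 93.2% |
| 0.9 | 5% | 28.28 | 91.9% |

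The last row is only a limit for VAS. With equal variances, σ = 29.02/√(2(1 − r)), which at r=0.9 is 64.9 mm. A 0–100 mm scale cannot have an SD above 50 mm.

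**4. Effect of a chance baseline difference.** If the arms differ by D at baseline, the change-score estimate shifts by −(1 − r)D. For D = 5 mm the shift is 3.5 mm at r=0.3, 2.5 mm at 0.5, 1.5 mm at 0.7 and 1.0 mm at 0.8. At r=0.5, σ is 29.0 mm and the standard error of the baseline difference with 60 per arm is 29.0 × √(2/60) = 5.3 mm, so a 5 mm difference is about one standard error. A 2.5 mm shift is 2.5/17.5 = 14% of the assumed effect.

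**5. Simulation check** (r=0.5, 60 per arm, 20,000 trials). The standard error of the treatment effect was 5.31 for the change-score t test and 4.63 for ANCOVA. The slope of the estimate on the baseline difference was −0.50 and 0.00 respectively. Both methods recovered the assumed 17.5 mm on average.

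**6. Methadone.** The article gives no SD and no expected effect for daily consumption. The ratio (1 + r)/2 applies if variances are equal, but no power can be computed.

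**The case against.** The strongest reply is that nothing is broken. The t test on change is unbiased under randomisation, its standard error already includes chance baseline variation, and the sample size was built for that comparison and reaches its stated power. All of this stands.

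Three further points also stand in part.

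- **Baseline is not ignored.** A reader might infer from the bare t test that it is. The methadone primary is defined as a change, results are summarised as mean change, and the sample size rests on VAS change. The section does not say outright that VAS is tested as change, but that is the most natural reading. A t test on raw week-6 scores would make the gain from ANCOVA look much larger, with variance lower by r² (64% at r=0.8). That reading contradicts the methadone definition and fits the VAS text poorly, so those figures should not be used.
- **The gain depends on r.** It shrinks as r rises. Participants have been on maintenance therapy for more than 30 days and the doctor controls the dose, so a high correlation for methadone is plausible, though this is inference. There the gain over change scores may be small.
- **The repeated-measures ANOVA is only exploratory.** A reader might take its interaction test for the primary analysis and object that it does not estimate a week-6 difference. The text gives it no such role, and does not say which visits enter it.

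A separate analysis plan may add covariates. The article nevertheless names the t test, so the point concerns a stated choice and not an omission.

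**Conclusion.** The concern holds as a matter of efficiency and robustness, not of validity. The planned comparison is sound and meets its power target for VAS on the protocol's own inputs; the documents do not support calling the trial biased or underpowered on this account. What is lost is precision, and protection against chance baseline imbalance.

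For VAS, ANCOVA would cut the variance by 35% to 10% for r between 0.3 and 0.8, and by 5% at r=0.9. This rests on equal variances at baseline and follow-up, on an assumed r, and on inputs stated for 4 weeks applied to a week-6 comparison. The extra power would be a useful reserve if dropout or the SD turns out worse than planned. For methadone the direction is the same but the size is unknown. The change is worth making because the data are already being collected.

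**What to change.** Amend the Statistical analysis section before unblinding:

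- For VAS, methadone consumption and the continuous secondary scales, replace the t test with ANCOVA at week 6, with the baseline value of the same outcome as covariate. Alternatively, use a mixed model with baseline as covariate and the week-6 arm contrast as the estimate. If the mixed model is chosen, state how it relates to the planned multiple imputation.
- Keep the independent-sample t test as an unadjusted sensitivity analysis, and say that it is on change from baseline.
- Leave the repeated-measures ANOVA exploratory, as already worded.

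The cost is a wording amendment to the protocol of a trial that is already recruiting, and one degree of freedom. No new data are needed.

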## Discussion

To our knowledge, JTN treatment for patients receiving MMT has not been intensively investigated. This study describes the protocol of a randomized controlled trial to test the effectiveness and safety of acupuncture as an adjunctive therapy for patients receiving MMT.

JTN, a type of acupuncture technique, has been practised for decades. One of the features of JTN is choosing treatment acupoints in a unique way. The prescription of JTN is comprised of several acupoint groups, and each acupoint group consists of three or four special acupoints that are based on local points, influential points or empirical points. The law of combination of these points may have more effectiveness to treat disease than a normal mixture of ‘cookbook’ points.

According to previous studies, the effectiveness of acupuncture as an adjunct therapy in patients receiving MMT has been controversial. Bearn reported a lack of effect for adjunctive MMT with auricular acupuncture upon withdrawal symptoms or drug craving [31]. Pei Lin showed a lack of effect for adjunctive MMT with auricular acupuncture upon the number of daily consumed cigarettes, withdrawal syndrome and relapse rate [32]. However, several studies have reported positive findings in the effectiveness of acupuncture for the treatment of drug dependence [33–35]. Chan claimed that 4 weeks of acupuncture as an adjunct to MMT may reduce the daily dosage of methadone and may cause a greater improvement in sleep latency [5]. Although JTN has been practised for several decades, this is the first time that JTN will be applied to treat opioid dependence. According to the theory of TCM, the acupoints we choose may help to tranquilize and free the body from tension, which may have the potential to ameliorate several mental or physical symptoms of opioid dependence.

One important limitation of our study is that it is an open-label trial, making it impossible to execute a blinding method. Patients may have strong treatment preferences for acupuncture, which may produce adjuvant treatment effects. To reduce this kind of bias, the acupuncturists and outcome assessors will be different, which will maintain the objectivity of assessment of outcomes. We will exclude the investigators and statisticians from randomization as well, to make sure all of them are blind to allocation.

In conclusion, the results of this trial will provide evidence on the effectiveness and safety of acupuncture as adjunctive therapy for patients receiving MMT.

## Trial status

This trial is currently recruiting patients, which started on 5 October 2019 and is anticipated to end on 1 December 2020. The protocol is Version 3.0 dated 2019/09/16.

## Data Availability

The full protocol of this study will be provided by the corresponding author. Datasets generated or analysed during the current study will be available from the corresponding author on reasonable request.

## Abbreviations

JTN: Jin’s three-needle acupuncture
TCM: Traditional Chinese medicine
DSM-V: Diagnostic and Statistical Manual of Mental Disorders, 5th edition
PSQI: Pittsburgh sleep quality index
BDI-II: Beck Depression Inventory-II
BAI: Beck Anxiety Inventory
DCOM: Daily consumption of methadone
MMT: Methadone maintenance therapy
AEs: Adverse events
CRFs: Case report forms
PP: Per-protocol
